**Fig. 1 Fig1:**
[figure not shown]
The PBF Nutrition Scheme. ‘PBF Nut’ means ‘Under PBF Nutrition programme besides the existing PBF scheme’ while ‘Comp Nut’ means input based financing compensation besides the existing PBF scheme

The intervention at nutritional HC and hospital levels started in January 2015, involving 45 nutritional HCs and 29 district hospitals with the extended PBF scheme, as well as 45 nutritional HCs with the compensation scheme (control group). The interventions in the other type of HCs as well as at the CHW level were expected to start in summer 2015, but due to major political instability since April 2015, they have started respectively only in January 2016 and in October 2015.

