## General objectives and research questions

The overarching objective of our research is to assess the effects of the introduction of criteria focusing on malnutrition prevention and care activities in the existing PBF system. Main research questions at 1) population and 2) HC levels are:Does the introduction of criteria focusing on malnutrition prevention and care activities in the existing PBF system result in a reduction in acute and chronic malnutrition rates in the community?Does the introduction of criteria focusing on malnutrition prevention and care activities in the existing PBF program result in better outcomes at the facility level, i.e. in better management of malnutrition cases (better recovery rates, shorter periods of treatment, etc.)?

In addition, the research incorporates two sub-questions which will allow identifying the possible causes of the success or any disappointing outcome, including unintended side-effects: Table 33)What are the transmission mechanisms induced by the introduction of criteria focusing on malnutrition prevention and care activities in the existing PBF program?4)What are the reasons for the success or failure of PBF on nutrition activities?

**Table 3 Tab3:** Main outcomes for the impact evaluation

Level	Outcomes
Population	- Prevalence of acute malnutrition (defined as WHZ < -2 or MUAC < 125 mm) and of stunting (defined as HAZ < -2) among children aged 6-23 months - WHZ, HAZ and MUAC among children aged 6-23 months
Health Centre	- Recovery rates from MAM and SAM cases of children below five years old - Duration of treatment of MAM and SAM cases of children below five years old

Notes: HAZ stands for Height-for-Age Z-score; MAM for Moderate Acute Malnutrition; MUAC for Mid-Upper Arm Circumference; SAM for Severe Acute Malnutrition; and WHZ for Weight-for-Height Z-score

In addition to these questions, the data collection has been designed in such a way to allow assessment of equity and efficiency of the intervention, potential externalities on other outcomes, and systemic spill-over effects, including possible demand for professional training by the health facilities. These aspects are not covered in this protocol paper.

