#### Sample size and randomization

The sample size of the household surveys is computed on the smallest difference in the main outcome that can be considered of public health significance, i.e. a reduction of about 25 % in acute malnutrition prevalence in intervention centres as compared to control centres. Assuming that the intervention will result in decreasing the prevalence of MAM in children aged 6–23 months from 10 % to 7.5 % [3], and assuming that 65 children aged 6–23 months are to be surveyed in the catchment area of each HC, 90 HCs were needed to be randomized to either the intervention or control group, for an α-error of 5 % and a β-error of 20 %. The number of children per HC was increased to 72 to allow for missing or incomplete data, amounting to a total of 6,480 children aged 6–23 months over the 90 selected HCs. In total, a sample of 6,480 children were surveyed for the baseline, and, two years after the start of the program, another sample of 6,480 children aged 6–23 months will be surveyed.

Selection of HCs invited to participate in the study was done by simple randomization (computer-based random selection) among the 193 eligible HCs, i.e. HCs providing nutrition services (treatment of SAM and MAM). The 90 selected HCs have been paired on essential parameters of organization and functioning in relation to the outcomes (MAM rehabilitation activity, volume of activity, population in the catchment area, and percentage of recovery among malnourished children) as measured during the baseline survey. This will then be used to control for the potential confounding effect of these parameters. Within each of the 45 pairs, allocation to the intervention was done randomly through a lottery system organized by the MoH during a workshop in December 2014.

Simple randomization should be applied to select the households to be surveyed in the catchment area of the 90 HCs. However, such an approach was difficult logistically and could have turned out to be extremely resource-consuming. The chosen alternative option was to sample clusters of households, i.e. households living close to each other. Six clusters of 12 eligible households were selected at random from the whole catchment area of a given HC. This could be done without expanding the overall sample size given the quite high intra-class correlation considered for the sample computation.

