#### Data collection tools

The household survey focuses on question (1) and collects information on the nutritional and health status of each selected child, as well as general information on their household (including socio-economics, food security variables). The health facility survey focuses on questions (2), (3) and (4). To get information on malnutrition recovery rates, a total of 24 individual clinical files randomly selected among the files of all children below five years old enrolled in the MAM care program (12 files) and in the SAM care program (12 files) during the last six months are transcribed. In addition, organizational aspects of the HCs as well as of the nutrition services are recorded through interviews to managers. To assess the quality of services, we combine two techniques: patient-provider observations carried out on six paediatric consultations (performed by a maximum of two HWs) and exit interviews at the end of each of these observed consultations, in order to get information on the satisfaction level as well as to record anthropometrics of the children. Finally, to assess knowledge of the observed HWs, we use vignettes to measure the practical knowledge on different tasks to perform: a pattern of consultation is proposed and the health worker can ask all the questions (related to history and physical exams) necessary to arrive at a diagnosis and propose a treatment. Three vignettes are administered to every health worker observed in consultation.

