#### Analysis strategy plan

First, some descriptive analysis are carried out in order to understand the main features of malnutrition management and of health services in general in Burundi at the HC level. Validation of the design was performed with the baseline survey data by comparing the treatment group with the control group.

Second, with both survey rounds’ data, the impact of the intervention will be assessed with multilevel statistical models with random effects at the HC level. Continuous dependent variables will be analysed in mixed-effect regression models, whereas categorical ones (e.g. recovery yes/no) will be analysed in logistic regression or Poisson regression models. At the population level, other factors of child malnutrition, such as household food security, socio-economic status, etc., will be controlled for. Interactions with season, child age and sex, stunting, and socio-economic parameters will be analysed. An equity analysis will also be performed in order to understand whether the intervention benefits more the poorer or richer households. At the HC level, other factors of child malnutrition recovery, such as for instance HC staff and CHWs knowledge and know-how, will be controlled for. Interactions with child age and sex, stunting and MUAC will be analysed.

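### The population-level stunting interaction uses a status measured after exposure that is itself a main outcome, so stratum effects are open to bias if the intervention changes stunting

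*Protocol article*

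**What the plan says.** The relevant statements in the protocol article are these.

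- Analysis strategy plan (quantitative component), directly after the population-level covariates and before the health-centre-level sentences: "Interactions with season, child age and sex, stunting, and socio-economic parameters will be analysed". Nothing limits stunting to a baseline or area-level value.
- Table 3, under General objectives and research questions, lists among the main population outcomes the prevalence "of stunting (defined as HAZ < -2) among children aged 6-23 months", and also HAZ itself. Research question 1 asks whether the scheme will "result in a reduction in acute and chronic malnutrition rates in the community".
- Sample size and randomization: "two years after the start of the program, another sample of 6,480 children aged 6–23 months will be surveyed".
- Implementation: "The intervention at nutritional HC and hospital levels started in January 2015".
- Data collection tools: the household survey "collects information on the nutritional and health status of each selected child".

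**The concern.** An effect modifier should be a characteristic that the intervention cannot have altered. Randomisation makes the two arms comparable overall. It does not make them comparable within groups defined by something that happened after allocation and that the intervention aims to change. If the scheme prevents some stunting, the children still stunted in the intervention arm are a different selection from the stunted children in the control arm, and the same holds for the non-stunted.

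The stake is the reading of the subgroup result. The evaluation is meant to inform national policy and other countries with similar schemes. A statement that the scheme works better, worse or not at all in stunted children could reflect who ends up in each stratum and not how they respond.

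**Working it through.** **1. Can a pre-intervention stunting value exist for a follow-up child?** The start was January 2015 and follow-up is two years later, so about January 2017. A child then under 24 months was born at about or after the start. The follow-up children are also a different sample from the baseline children. A child-level baseline value therefore cannot exist. The only child-level stunting value is the one taken in the follow-up household survey, which also supplies WHZ, MUAC and HAZ.

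**2. Uniform HAZ shift, effect on the WHZ strata.** Assumptions: 58 % stunted in controls (the Background figure for under-fives, used as a proxy for 6–23 months), normal HAZ with SD 1.2, HAZ–WHZ correlation ρ of 0.2 to 0.3, WHZ SD 1.1, and no true effect on WHZ. Apparent WHZ effect in a stratum = 1.1 × ρ × change in the truncated standard-normal mean when the cut-off moves from 0.202 to 0.202 − shift/1.2.

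| HAZ gain | ρ | Stunted | Non-stunted | Difference (absolute) |
|---|---|---|---|---|
| 0.20 | 0.2 | −0.022 | −0.024 | 0.002 |
| 0.20 | 0.3 | −0.034 | −0.036 | 0.003 |
| 0.30 | 0.2 | −0.034 | −0.036 | 0.002 |
| 0.30 | 0.3 | −0.051 | −0.054 | 0.003 |

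Differences are taken before rounding. With 45 × 65 = 2,925 children per arm and no clustering, each stratum standard error is √(2 × 1.1² / (2,925 × p)): 0.038 for p = 0.58 and 0.044 for p = 0.42. The interaction standard error is √(0.038² + 0.044²) = 0.058. So here the false interaction is about one-twentieth of a standard error. The stratum effects are displaced by roughly 0.6 to 1.4 unclustered standard errors. A negative correlation reverses the sign.

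**3. Stunting effect that differs between children.** Assumptions: two equal frailty classes; acute malnutrition 5 % and 15 % in controls (mean 10 %, the sample-size figure); stunting 38 % and 78 % in controls (mean 58 %); true risk ratio 0.75 in every child, so no real effect modification. The control risk in stunted children is (0.05 × 0.38 + 0.15 × 0.78) / (0.38 + 0.78) = 0.117; in non-stunted it is (0.05 × 0.62 + 0.15 × 0.22) / (0.62 + 0.22) = 0.076. Intervention-arm risks use the changed stunting proportions and are multiplied by 0.75.

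| Stunting under intervention (less frail, frailer) | RR stunted | RR non-stunted | Ratio |
|---|---|---|---|
| 38 %, 78 % (unchanged) | 0.75 | 0.75 | 1.00 |
| 28 %, 78 % | 0.79 | 0.72 | 1.09 |
| 20 %, 78 % | 0.83 | 0.70 | 1.18 |
| 38 %, 58 % | 0.71 | 0.89 | 0.79 |

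With no effect on acute malnutrition at all, the second row gives 1.05 and 0.96, and the fourth gives 0.94 and 1.19. A false interaction can arise in either direction, and none arises if stunting is unchanged.

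**4. If the interaction were also applied to HAZ.** With 58 % stunted and SD 1.2, the control mean is −2 − 1.2 × 0.202 = −2.24. A uniform gain of 0.20 z lowers stunting to 51.4 %. Mean HAZ among the stunted moves from −3.051 to −2.973 (0.078 z) and among the non-stunted from −1.125 to −1.058 (0.068 z). The true 0.20 z thus appears as about 0.08 and 0.07 z. SDs of 1.0 and 1.4 give 0.077 to 0.079 and 0.067 to 0.068.

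**The case against.** The strongest reply has four parts.

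*The bias is conditional.* It arises for WHZ, MUAC and acute malnutrition only if the scheme shifts stunting. Many of the paid services concern acute malnutrition, and the community and referring-centre components started only in October 2015 and January 2016. This stands as a limit on certainty. A reader might infer that the subgroup effects are simply biased; the documents support only that they are open to bias, of unknown direction. The condition is nonetheless the trial's own hypothesis in research question 1.

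*Under a uniform shift there is almost no false interaction.* This is correct, as step 2 shows. A reader might infer that any reported difference between stunted and non-stunted children must be an artefact. That does not follow. A material false interaction needs a stunting effect that differs between children, as in step 3, and those values are assumed.

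*The article does not say that stunting will be crossed with HAZ.* It gives one list of interactions for all population outcomes. A reader might infer that over 60 % of a HAZ effect will be lost; this holds only if that circular model is fitted, and the text does not spell it out.

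*The word could mean area-level baseline stunting, with the detail left to a fuller document.* The wording does not exclude that. But stunting stands in the list beside child age and sex with no such qualifier, and the one benign child-level reading, baseline status, is impossible by step 1.

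**Conclusion.** The point holds in a limited form. As worded, the population-level plan includes an interaction with a variable that is a main outcome and that, at child level, can be observed only after exposure and alongside the outcome. If the intervention changes stunting, the strata are not comparable between arms, and stratum effects on WHZ, MUAC or acute malnutrition may be wrong in either direction. The illustrations put this at 0.02 to 0.05 z for WHZ under a uniform shift, with a negligible interaction. With a stunting effect confined to one frailty class, the ratio of stratum risk ratios is 0.79 to 1.18 when the truth is 1.00. Applied to HAZ or stunting itself, the interaction would be circular.

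These sizes rest on assumed SDs, correlations, HAZ gains and frailty classes, and on the under-fives figure of 58 %. The overall effect estimates, the sample size and the interactions with season, age, sex and socio-economic parameters are untouched. The stunting interaction in the health-centre-level models is a separate matter and is not judged here.

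**What to change.** Remove current child-level stunting as an effect modifier from the population-level models and analyse it only as an outcome. Any cross-tabulation of stunting with acute malnutrition should be labelled descriptive.

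If the question is whether the scheme works differently where chronic malnutrition is common, use the baseline-survey stunting prevalence of each health-centre catchment as the modifier, and confirm that the household measurements preceded the December 2014 lottery. The article says the pairing parameters came from the baseline survey but does not date the household anthropometry.

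The cost is one line of analysis text, with no new data collection. The downside should be stated with it. The question becomes an area-level one with 90 values, each from about 72 children, with a standard error of √(0.58 × 0.42 / 72) = 0.058, about 6 percentage points before clustering. The interaction will therefore be attenuated and imprecise.

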#### Theory of change

The introduction of nutrition activities into the PBF program translates policy makers’ belief that PBF can trigger some positive changes in the performance of the health personnel, facilities or system which will eventually impact on households and children. We have identified seven tracks for transmission of effects for the health facility performance:**The income track**: the injection of extra financial resources might have a positive effect on nutrition services, as it allows the health facility manager to recruit more staff, to better equip his facility, etc.**The cash track**: the fact that the financial resources are transferred directly to the health facility’s bank account allows the latter to rapidly and autonomously spend.**The incentive track**: the extra resources are conditioned upon higher performance in nutrition activities; this should motivate community actors and staff to improve their performance in order to boost the health facility’s income and theirs (if bonuses are distributed among HWs). At facility level, the effect on other services is unclear: it can be negative for some (e.g. if the staff in charge of nutrition used to be responsible for other services which are now overlooked, as they are relatively less financially rewarding) and positive for others (if there are economies of scope—i.e. dedicating efforts to nutrition activities, reduce efforts required for other activities, thanks to synergies).**The information track**: through the contract, the fee system and the related information sessions, staff have a clearer view on what performance should be, as far as nutrition services are concerned. Feedback from the program may also guide their decisions to improve. We hypothesize a positive effect on nutrition services. However, as for the incentive track, a negative effect could be that activities which are not remunerated may be perceived as non-important.**Supervision & enforcement track**: under the new scheme, verification is extended to nutrition activities; this means that there will be more interaction between supervisors and the personnel in charge of nutrition. On top of the possible subsequent transfer of information (e.g. advice on good practices), the supervision may activate interpersonal motivators.**Culture at provider level track**: a PBF scheme invites health facility managers to develop a work culture more favourable to innovation, flexibility, responsibility and entrepreneurship. As PBF has been a national policy for five years, one can assume that this is already the case in Burundi. However, one cannot exclude that it could positively influence the nutrition department more.**Health system track**: it has been argued that PBF can trigger several system effects [16]. Here, part of these effects might come from the supervisors of the impact evaluation (e.g. the MoH requesting UNICEF and the WFP to better supply nutrition inputs; the WB solving some problems which may affect the study). Another part might come from the health facilities themselves (e.g. pressure upon the Department for Nutrition within the MoH to be a more reliable and responsive supplier). We expect that CHWs will refer more malnourished children to HCs and HCs will refer more SAM children to referral hospitals. This may trigger some unexpected feedback loops.

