**Fig. 2 Fig2:**
[figure not shown]
Results chain of the introduction of nutrition criteria in the PBF grid

There is also a specific theory of change for the control HCs. The main design difference between the intervention and control groups is the formula to obtain the extra funding: each HC of the intervention group has to improve its own performance to increase its revenue; control HCs do not have any effort to do: they just have to hope that the intervention group, as a whole, will be performing. This choice for the definition of the two groups to compare indicates that the main causal path under investigation is the incentive one. Other tracks are not denied (see the qualitative part of the research) but are considered as secondary Table 2.

**Table 2 Tab2:** Routes applying in the Intervention and Control groups at the facility level

	Intervention group	Control group
(1) Income	++	++ ^a^
(2) Cash	++	++ ^a^
(3) Incentive	++ on nutrition services ? on other services	~
(4) Information	++	+ ^b^
(5) Supervision & enforcement	++	? ^c^
(6) Culture at provider level	~ or +	~ or + ^d^
(7) Health system	++	? ^e^

Notes: Symbols + and ++ mean that routes apply moderately to strongly; ? means unclear, ~ means neutral ^a^The control HCs will get additional financial resources which will correspond to a weighted average of the nutrition subsidies received in the intervention group. ^b^Before the start of the intervention, all 90 HCs were provided with some information on the nutrition indicators and on their performance in nutrition services. ^c^In a district where there are control and intervention HCs, the district team supervisors may transfer good practices to both intervention and control HCs. ^d^Control HCs know that there will probably be a scale up of the nutrition indicators to all HCs after the pilot; some managers may anticipate this by already reorganizing their nutrition services. ^e^Some health system effects might affect control HCs (e.g. if there is a problem of availability of nutritional inputs at national level, because of the pressure by intervention HCs, the supply to control HCs may be reduced)

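### The health-centre impact model controls for staff and community health worker knowledge without limiting it to baseline; follow-up knowledge may be a mediator, so the total effect asked for in question 2 would not be estimated

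*Protocol article*

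**What the plan says.** In the quantitative Analysis strategy plan, with data from both survey rounds, "the impact of the intervention will be assessed with multilevel statistical models with random effects at the HC level". For the HC-level outcomes, other factors of recovery, "such as for instance HC staff and CHWs knowledge and know-how, will be controlled for". The text does not say from which round the knowledge value is taken, and does not present this as a secondary or mediation analysis.

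The Theory of change section describes an information track, by which "staff have a clearer view on what performance should be, as far as nutrition services are concerned", and a supervision track: "On top of the possible subsequent transfer of information (e.g. advice on good practices), the supervision may activate interpersonal motivators". Table 2 rates the information route ++ in the intervention group and + in the control group. A note to that table adds: "Before the start of the intervention, all 90 HCs were provided with some information on the nutrition indicators".

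Research question 2 asks whether introducing the criteria will "result in better outcomes at the facility level, i.e. in better management of malnutrition cases". Transmission mechanisms are a separate question, number 3.

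For the population-level models the same section says: "Interactions with season, child age and sex, stunting, and socio-economic parameters will be analysed". Table 3 lists among the population outcomes the prevalence of acute malnutrition "and of stunting (defined as HAZ" below −2, in children aged 6 to 23 months.

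**The concern.** Question 2 asks for a total effect: what happens to recovery and treatment duration when the criteria are introduced, by whatever route. A covariate that the intervention can change after randomisation does not belong in the model for that effect. If better-informed staff are one way in which the scheme works, holding their follow-up knowledge constant subtracts that route from the estimate.

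It also creates a second problem. Knowledge is not randomised, so anything unmeasured that affects both knowledge and recovery (management quality, for example) can enter the treatment comparison once knowledge is conditioned on. Randomisation does not protect against this.

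A scheme that works partly through knowledge could therefore be reported as weaker than it is, or as having no demonstrable effect, on the HC-level question that the study was set up to answer.

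**Working it through.** **1. Is knowledge on the declared causal path?**
- The information and supervision tracks both describe staff learning something as a result of the scheme.
- Table 2 ranks the information route higher in the intervention group. For supervision, the control entry is a question mark, defined as unclear.
- The Implementation section places community health worker (CHW) groups under nutrition PBF in the intervention group only. That component began in October 2015, after allocation in December 2014.
- HC health-worker knowledge is measured with vignettes in the facility survey, and HCs are surveyed at baseline and follow-up. A follow-up score is thus a post-randomisation variable that the intervention may change.

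**2. Reproducing the plan's own HC-level figure.** Inputs from the sample-size section: recovery 80% against 90%, α 5% (two-sided assumed), power 80%, ICC 0.15, 45 HCs per arm, 12 files per HC and service.
- Individually randomised size per arm: n = [1.96·√(2·0.85·0.15) + 0.8416·√(0.16 + 0.09)]² / 0.10² = 199.
- Files per HC: solve 45m = n·[1 + (m − 1)·0.15]. This gives m = 199·0.85 / (45 − 199·0.15) = 169.15 / 15.15 = 11.2, so 12. The stated figure reproduces.
- At m = 12 the design effect is 1 + 11·0.15 = 2.65, and the effective size is 540 / 2.65 = 203.8 per arm. Power is 80.9%.

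**3. Effect of adjusting for follow-up knowledge.** The mediated share s is an assumption; the documents give none. On the risk scale, the adjusted coefficient targets d = 0.10·(1 − s). With p₁ = 0.80, p₂ = 0.80 + d, p̄ their mean and n = 203.8:

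Power = Φ{ [d − 1.96·√(2p̄(1 − p̄)/n)] / √[(p₁(1 − p₁) + p₂(1 − p₂))/n] }

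| Assumed share s | Target d (points) | Power |
|---|---|---|
| 0% | 10 | 81% |
| 10% | 9 | 71% |
| 20% | 8 | 60% |
| 30% | 7 | 48% |
| 50% | 5 | 26% |

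These powers ignore any precision gained from the covariate.

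**4. Check by simulation.** A linear model at cluster level, 45 HCs per arm, true total effect 10 points, 4,000 replicates per setting. Mean estimates in points:

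| Share | Adjusted for baseline knowledge | Adjusted for follow-up knowledge | Follow-up knowledge, with an assumed unmeasured common cause |
|---|---|---|---|
| 0% | 10.0 | 10.0 | 10.1 |
| 10% | 9.9 | 8.9 | 8.5 |
| 20% | 10.0 | 8.0 | 7.0 |
| 30% | 10.0 | 7.0 | 5.4 |
| 50% | 9.9 | 4.9 | 2.2 |

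Baseline adjustment leaves the total effect intact. In the last column the common cause raises both knowledge and recovery, which deepens the loss; a common cause acting on them in opposite directions would push the other way.

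**5. Stunting, population-level model only.** Stunting is a main outcome, and the follow-up survey draws a new sample of children. A treatment-by-stunting interaction in that sample splits children by something the intervention is meant to change. The subgroups need not be comparable between arms.

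**The case against.** The strongest reply is that the round is not stated. If only baseline knowledge were entered, the bias would vanish, as the simulation shows, and a condensed article may leave such detail to a fuller plan. This stands in part. But the article does fix the covariate, places it in a model that uses both rounds, and describes it as a factor of recovery. The natural reading is the value at each round, and nothing in the text excludes it.

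Second, the vignettes test history-taking, examination, diagnosis and treatment, whereas the information track is about knowing what performance is expected. The two overlap only partly. The article also names the incentive track as the main path and the others as secondary. Both remarks argue for a small mediated share, but neither makes it zero.

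Three stronger readings are tempting and are not supported:
- A reader might infer that the estimate is certainly biased towards no effect, by a known amount. The shares are assumptions, the direction can differ under confounding, and the point figures assume additivity on the risk scale, whereas logistic or Poisson models are planned.
- A reader might take Table 2 to rate supervision lower in the control group. It marks it as unclear, and a note says that supervisors may pass good practices to both groups.
- A reader might extend the stunting point to the HC-level interactions. There stunting would describe a treated child, and the article does not say when it is measured. At population level the interaction affects only the subgroup reading, not the main effect estimate.

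**Conclusion.** The point holds in a limited form. As written, the plan permits follow-up knowledge in the main HC-level impact model, and on the protocol's own theory of change that variable may be a mediator. The resulting coefficient would not be the total effect asked for in question 2.

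The documents do not allow the size to be determined. Assumed shares of 10 to 50% correspond to a reported gain of about 9 to 5 points instead of 10, and to power of about 71% to 26% instead of 81%. With no mediation there is no attenuation. The population-level models are not affected by the knowledge covariate. The stunting interaction is a separate, lesser matter of interpretation.

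**What to change.** - In the main HC-level models, adjust only for the pairing and for baseline HC values: the baseline outcome and the baseline health-worker vignette scores. Include CHW knowledge only if it was measured at baseline; the article describes no instrument for it.
- Use follow-up knowledge only in a separate mediation analysis under question 3, with its assumptions about confounding stated.
- At population level, replace the treatment-by-stunting interaction with one on baseline stunting prevalence in the HC's catchment area, which the baseline household survey can supply, or label the present one descriptive.

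The cost is a change of wording in the analysis plan, to be made before follow-up data are analysed. No new data are needed for the pairing, the baseline outcome, the vignette scores or baseline stunting. This cannot be said for CHW knowledge.
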